#### Outcome Evaluation and Justification of the Sample Size

The following discussion focuses on IH data. The cases with KPSC and UWM data are similar. We will employ McNemar test to compare the paired-sample outcomes reached by the 2 predictive models mentioned in Aim 1’s accuracy evaluation section. We will test 2 hypotheses: using our techniques will link to a potential drop in (1) inpatient stays and (2) emergency room visits in the subsequent year. Our primary hypothesis is as follows:

Null hypothesis: The number of inpatient stays in the subsequent year reached by the first model is the same as that reached by the second.Alternative hypothesis: The number of inpatient stays in the subsequent year reached by the first model is smaller than that reached by the second.

Among the patients truly at high risk for future hospital use, the first model will find some missed by the second and vice versa. Assuming the former cuts inpatient stays in the subsequent year by 5% and the latter increases them by 1%, at a one-sided significance level of 0.05, a sample size of 251 instances provides 80% power to verify the primary hypothesis. The IH data in the 13th year cover about 35,000 COPD patients, offering enough power to test the primary hypothesis.

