## Introduction

### Three Major Gaps in the Current Predictive Modeling Method for Implementing Care Management

COPD and asthma are chronic respiratory diseases incurring heavy health care burdens on society, health care systems, and payers. In the United States, COPD affects over 6.5% of adults, is the third leading cause of death, and incurs 700,000 inpatient stays, 1.5 million emergency room visits, and US $32 billion in cost annually [1]. Asthma affects 8% of adults [2] and 9.6% of children [3,4] and incurs 3630 deaths, 493,000 inpatient stays, 1.8 million emergency room visits, and US $56 billion in cost annually [2,5]. As a service intended to prevent poor outcomes such as hospitalization, care management is widely adopted to provide tailored preventive care for COPD and asthma patients. Purchased by most large employers and offered by almost all private health plans [6-8], care management is a collaborative process to evaluate, plan, implement, coordinate, and monitor options and services to accommodate an individual’s health and service needs [9]. In care management, a care manager calls a patient regularly, helps arrange for medical appointments, and schedules health and related services. Appropriate use of care management can cut hospital use (emergency room visits and inpatient stays) by up to 40% [7,10-15], lower cost by up to 15% [11-16], and enhance patient adherence, quality of life, and satisfaction by 30% to 60% [10].

Predictive models are widely used, for example, by health plans in 9 of 12 regions [17], as the best method [18] to warn of poor outcomes and to identify COPD and asthma patients for care management [6-8]. Multiple models have been built for predicting the health outcomes of individual COPD and asthma patients [19-28]. However*,* current modeling methods have 3 major gaps restricting their effectiveness owing to inadequate use of temporal features showing trends and early health change. A temporal feature, such as the slope of pulmonary function across the last year, is an independent variable formed by transforming longitudinal attributes.

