#### Outcomes of the Number of Inpatient Stays and the Number of Emergency Room Visits in the Subsequent Year and the Estimation Approach

The number of inpatient stays in the subsequent year is the primary outcome. The number of emergency room visits in the subsequent year is the secondary outcome. The following discussion focuses on IH data and inpatient stays. The cases with KPSC and UWM data and/or emergency room visits can be handled similarly. From statistics reported in the literature [102,103], we will obtain the percentage of inpatient stays, *p,* a care management program can help avoid. Given a set of variables, we will adopt the same method used in Aim 1 to train a predictive model on the data in the first 12 years. For the data in the 13th year, we will gather prediction results, then estimate the outcome. Consider a patient who will have *n_e_* inpatient stays in the subsequent year without enrolling in the program. If the patient gets enrolled, for each inpatient stay of the patient, we will simulate whether it will occur or not based on probability 1-*p*. The gross outcome estimate will be the sum of the estimated outcomes of all patients. Adopting a similar method, we will find the minimum accuracy required for the predictive model to be valuable in clinical practice.

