#### Performance Evaluation

We will compare the association rules obtained from IH, KPSC, and UWM data. The following discussion focuses on IH data. The cases with KPSC and UWM data are similar. We will do analyses similar to those in Aim 1 to compare using our new techniques in Aim 4 versus the current method of offering no explanation. We will compare the outcomes of the number of inpatient stays and the number of emergency room visits in the subsequent year and the accuracy reached by the 2 models: the best ones produced in Aims 1 and 4. We will test 3 hypotheses: using our new techniques in Aim 4 will link to a potential drop in (1) inpatient stays and (2) emergency room visits in the subsequent year and (3) boost prediction accuracy. Our primary hypothesis is as follows:

Null hypothesis: The number of inpatient stays in the subsequent year reached by the second model is the same as that reached by the first.Alternative hypothesis: The number of inpatient stays in the subsequent year reached by the second model is smaller than that reached by the first.

We will employ McNemar test to compare the paired-sample outcomes reached by the 2 models.

Among the patients truly at high risk for future hospital use, the second model will find some cases missed by the first and vice versa. Assuming the former cuts inpatient stays in the subsequent year by 2.5% and the latter increases them by 0.5% and using McNemar test, at a one-sided significance level of 0.05, a sample size of 503 instances provides 80% power to verify the primary hypothesis. The IH data in the 13th year cover approximately 35,000 COPD patients, offering enough power to test the primary hypothesis.

To assess our technique’s impact on model generalizability, we will compare 2 predictive models’ accuracy on KPSC/UWM data. The first model is the best one produced in Aim 1 on IH data using the variables available in both the IH and KPSC/UWM datasets. The second is produced by using our technique to drop uninformative features from the first model and retrain it on IH data. We will develop and test our techniques on asthma as well.

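### Aims 3 and 4 test a simulated number of inpatient stays with McNemar's test, which does not fit the stated hypothesis and makes the p-value depend on the assumed avoidance rate and the random draw

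*Protocol article*

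**What the plan says.** Under Aim 3, the section on outcomes and the estimation approach defines a count: "The number of inpatient stays in the subsequent year is the primary outcome". Emergency room visits are the secondary outcome. The count is partly simulated. The avoidable share p comes from outside the study ("From statistics reported in the literature [102,103], we will obtain the percentage of inpatient stays"), and if a patient would be enrolled then "for each inpatient stay of the patient, we will simulate whether it will occur or not based on probability" 1-p. Results are then added up: "The gross outcome estimate will be the sum of the estimated outcomes of all patients".

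The Aim 3 section on outcome evaluation and sample size names the test ("We will employ McNemar test to compare the paired-sample outcomes reached by the 2 predictive models") and states the null hypothesis in terms of counts: "The number of inpatient stays in the subsequent year reached by the first model is the same as that reached by the second". It assumes a 5% cut in stays against a 1% increase, and gives 251 instances for 80% power at a one-sided 0.05 level, set against about 35,000 COPD patients.

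Aim 4, Performance Evaluation, has the same primary outcome and again: "We will employ McNemar test to compare the paired-sample outcomes reached by the 2 models". There the assumptions are 2.5% against 0.5%, giving 503 instances. Aim 4 does not restate the simulation.

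The article gives no value for p in Aims 3 and 4. The nearest figure is in the Introduction: "Appropriate use of care management can cut hospital use (emergency room visits and inpatient stays) by up to 40" per cent. The Aim 3 sensitivity analysis varies the sets of variables, not p.

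**The concern.** Two separate matters arise.

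The first is fit. McNemar's test compares two proportions from independent yes/no pairs. The stated hypothesis compares numbers of stays, and a patient may have several. The sample size text does not settle the unit: its percentages refer to stays, its sample size to instances, and the available sample to patients.

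The second is what the test statistic contains. Once both models are trained, the information on which is better lies in which stays belong to patients that each model would enrol. Deleting a random fraction p of those stays adds nothing to it. The p-value then depends on a literature constant and a random seed as well as on the models, and the primary conclusions of Aims 3 and 4 rest on it.

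**Working it through.** **1. The plan's own figures.** Exact one-sided McNemar test at 0.05, with power summed over the number of discordant pairs, Binomial(n, total discordance):

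- 5% against 1%: power 0.8002 at n = 251 and 0.7984 at n = 250.
- 2.5% against 0.5%: power 0.8001 at n = 503 and 0.7992 at n = 502.

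Both sizes reproduce, for independent binary pairs.

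**2. If the pair is the patient.** The count must become a yes/no outcome, most naturally any stay or none. Take an enrolled patient with n stays, and p = 0.4 as an illustration. Expected stays avoided are n x p; the chance of moving to no stay is p^n.

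- n = 1: 0.4 stays avoided; chance 0.4.
- n = 3: 1.2 stays avoided; chance 0.4^3 = 0.064.

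The stated hypothesis gives the frequent user three times the weight of the single-stay patient. The dichotomised test gives about a sixth (0.064/0.4 = 0.16). It therefore answers a different question.

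**3. If the pair is the stay.** All stays of one patient share that patient's enrolment status, so pairs are not independent. Simulation under a true null, with these assumptions: 100 differently enrolled patients, each equally likely to be enrolled by either model alone; geometric stay counts with a minimum of one; p = 0.4; draws shared between models; 40,000 runs; nominal one-sided 5%.

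| Mean stays per patient | z test | Exact test |
|---|---|---|
| 1 | 5.0% | 3.8% |
| 1.5 | 8.1% | 6.7% |
| 2 | 11.1% | 9.5% |
| 3 | 15.2% | 14.0% |

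The inflation itself changes with p: at mean 2 the z test rejects 6.5% at p = 0.1.

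**4. Effect of p with the models fixed.** Let B and C be the stays captured by model 1 only and by model 2 only. With shared draws the expected discordant counts are b = pB and c = pC, so

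z = (b - c)/sqrt(b + c) = sqrt(p) x (B - C)/sqrt(B + C).

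With assumed B = 100 and C = 60, and a critical value of 1.645:

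- p = 0.10: (10 - 6)/sqrt(16) = 1.00
- p = 0.40: (40 - 24)/sqrt(64) = 2.00
- captured stays compared directly: 40/sqrt(160) = 3.16, before allowing for clustering

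If stays of patients enrolled by both models (assume S = 500) are drawn separately for each model, p(1 - p)S = 0.4 x 0.6 x 500 = 120 is added to both b and c. At p = 0.40, z = (160 - 144)/sqrt(304) = 0.92.

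**5. Effect of the seed.** With the same 100 and 60, p = 0.4 and shared draws, 40,000 repetitions gave exact one-sided p-values from 0.0004 to 0.35 (central 95%). About 62% were at or below 0.05.

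**6. Do the draws alone create false positives?** Null case with 160 differently enrolled patients, one stay each, 200,000 runs: the z test rejects 4.9%, 4.9% and 5.0% at p = 0.1, 0.2 and 0.4. They do not.

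**7. At the planned effect sizes.** Aim 2 gives about 2000 COPD patients who used IH hospitals in the 14th year. That includes emergency visits, so it is an upper figure. Applying the planned percentages to it (an assumption):

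- Aim 3: 100 against 20, z = 80/sqrt(120) = 7.3.
- Aim 4: 50 against 10, z = 40/sqrt(60) = 5.2.

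If p were a quarter of what these imply, z would halve to 3.65 and 2.58. Adding the 120 of step 4 to the unscaled counts gives 80/sqrt(360) = 4.2 and 40/sqrt(300) = 2.3. All exceed 1.645.

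**The case against.** The strongest reply is that the simulation costs power, not validity, and step 6 bears this out. A reader might infer that the p-values are invalid however the test is run. The documents do not support that: error inflates only if the pair is the stay, and setting 251 and 503 against 35,000 patients suggests that the patient is meant. What remains on that reading is a dichotomisation which a condensed article might leave to a fuller document. It would still be a test of a hypothesis other than the one printed.

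A reader might also infer that significance would flip in the actual study. The 100, 60 and 500 are illustrative and lie near the critical value; at the planned effects the result may well stay significant (step 7). Nor are 251 and 503 miscalculated.

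The article does not give the number of simulation runs or say whether draws are shared between models, so the seed figures assume one run and 0.92 assumes separate draws. Averaging many runs would remove the noise, but leaves fractional outcomes to which McNemar's test does not apply.

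The extension to Aim 4 is inference. It is a fair one: Aim 4 tests a potential drop in stays between two models on past data, and no other way of generating that outcome is described.

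Finally, this is a retrospective simulation, and the Discussion leaves impact to later randomised trials. That lowers the severity.

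**Conclusion.** The point stands as a should-fix. The stated test does not match the stated hypothesis on either choice of pair. With the patient as pair, the number of stays is not what is tested. With the stay as pair, type I error was about 8% to 15% at nominal 5% (z test, p = 0.4, assumed geometric stay counts with mean 1.5 to 3). On both, the draws add noise and p rescales the statistic, which costs power and makes the p-value depend on p and on the seed. For single-stay patients, or with the stay as pair, z is proportional to sqrt(p). The size of that effect in this study is unknown, because p and the enrolment overlap are not given.

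**What to change.** In Aims 3 and 4, replace the random draws by their expectation: avoided stays = p x stays of the patients a model would enrol. Test the difference in captured stays between the two models' enrolled patients with a patient-level paired bootstrap or permutation test. Because p multiplies the difference and its null distribution alike, it cancels, and resampling whole patients handles repeated stays. Treat emergency room visits in the same way.

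Report expected avoided stays over a stated range of p as a descriptive table. Restate the 251 and 503 justifications for the new test, in a single unit. State in Aim 4 that the Aim 3 outcome definition applies.

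The cost is a few sentences in two sections and a new power statement. No new data are needed, and computing should be lighter than the simulation.

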### Aim 4: Automatically Identify Actionable Temporal Risk Factors for Each Patient at High Risk for Future Hospital Use and Assess the Impact on Prediction Accuracy and Outcomes

Care managers currently give finite input on the patient to the other clinical care team members. Owing to bandwidth constraints, care managers can afford to examine only a finite number of patients top ranked by the predictive model—those whose projected risk for future hospital use is over a given threshold like the 95th percentile. For those patients, we will automatically explain early warnings, identify actionable temporal risk factors, and suggest tailored interventions. This helps care managers make enrollment decisions and form tailored care plans. This also enables care managers to pass actionable information on to the other members in the clinical care teams and collaborate more closely with them. To implement the new function, we will improve our previous method [59] to automatically explain a machine learning model’s prediction results without incurring any accuracy loss. For nonlongitudinal tabular data, our previous method separates explanation and prediction by employing 2 models simultaneously, each for a distinct purpose. The first model gives predictions to maximize accuracy. The second employs class-based association rules mined from historical data to explain the first model’s results. Our previous method cannot handle longitudinal attributes and has not yet been applied to COPD, asthma, or care management.

As mentioned in Aim 1, we will use temporal features to convert longitudinal data to tabular data, with 1 column per feature. Then we can apply our previous automatic explanation method [59]. Each patient is represented by the same set of features and is marked as either high risk for future hospital use or not. From historical data, our method mines association rules linked to high risk. An example rule is as follows: the ratio of inhaled steroid to beta agonist dispensing to the patient decreased over 12 months AND sulfur dioxide level was ≥3 parts per million for ≥5 days in the past week ⟶ high risk. The first item on the left-hand side of the rule is an actionable temporal risk factor. Two interventions for the first item are to (1) assess COPD controller medication compliance and change, prescribe, or raise the dose of the medication if needed and (2) assess the patient for COPD triggers and ensure the patient stays away from them. Our paper [71] listed several interventions for a few other temporal risk factors. By discussion and consensus, the clinical experts in our team will check the mined rules and drop those making little or no sense clinically. For every rule that remains, our clinical team will mark the actionable temporal risk factors in it and list zero or more interventions that address the reason shown by the rule.

At the time of prediction, for every patient our most accurate model projects to be at high risk for future hospital use, we will find and show all of the association rules whose left-hand side conditions the patient satisfies, and list the interventions linking to these rules as our suggestions. Each rule shows a reason why high risk is anticipated for the patient. Users of our automatic explanation function can give feedback to help us find and drop unreasonable rules [64].

#### Performance Evaluation

We will compare the association rules obtained from IH, KPSC, and UWM data. The following discussion focuses on IH data. The cases with KPSC and UWM data are similar. We will do analyses similar to those in Aim 1 to compare using our new techniques in Aim 4 versus the current method of offering no explanation. We will compare the outcomes of the number of inpatient stays and the number of emergency room visits in the subsequent year and the accuracy reached by the 2 models: the best ones produced in Aims 1 and 4. We will test 3 hypotheses: using our new techniques in Aim 4 will link to a potential drop in (1) inpatient stays and (2) emergency room visits in the subsequent year and (3) boost prediction accuracy. Our primary hypothesis is as follows:

Null hypothesis: The number of inpatient stays in the subsequent year reached by the second model is the same as that reached by the first.Alternative hypothesis: The number of inpatient stays in the subsequent year reached by the second model is smaller than that reached by the first.

We will employ McNemar test to compare the paired-sample outcomes reached by the 2 models.

Among the patients truly at high risk for future hospital use, the second model will find some cases missed by the first and vice versa. Assuming the former cuts inpatient stays in the subsequent year by 2.5% and the latter increases them by 0.5% and using McNemar test, at a one-sided significance level of 0.05, a sample size of 503 instances provides 80% power to verify the primary hypothesis. The IH data in the 13th year cover approximately 35,000 COPD patients, offering enough power to test the primary hypothesis.

To assess our technique’s impact on model generalizability, we will compare 2 predictive models’ accuracy on KPSC/UWM data. The first model is the best one produced in Aim 1 on IH data using the variables available in both the IH and KPSC/UWM datasets. The second is produced by using our technique to drop uninformative features from the first model and retrain it on IH data. We will develop and test our techniques on asthma as well.

### Aim 5: Assess Actionable Information’s Impact on Clinicians’ Acceptance of Early Warnings and on Perceived Care Plan Quality

As an essential preparatory step for future clinical deployment, we will evaluate actionable information’s impact on UWM care managers and physicians’ decision making in a test setting. For physicians, we will use primary care physicians, pulmonologists, and allergists managing COPD patients. The discussion below focuses on care managers. The case of evaluating with 10 physicians is similar.

#### Subject Recruitment

As an operational project at UWM, we are working on COPD outcome prediction and can access approximately 25 UWM care managers for adults. By making announcements in their email lists and personal contact, we will recruit 10 care managers. We will adopt purposeful sampling to ensure adequate variability in work experience [106]. All evaluation test participants will give consent and be up-to-date on privacy and information security policy training required by UWM. Participants will obtain pseudonyms, connecting their responses to questions to protect privacy. After completing the task, each will obtain US $2400 as compensation for participation for approximately 40 hours of work. We will conduct 2 experiments.

### Experiment 1

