#### Procedures

From the IH data in the 13th year, we will randomly select 400 IH COPD patients who used the hospital in the subsequent year and automatically explain the prediction results of the best IH model built in Aim 4. We will use patients outside of UWM to help ensure no care manager is aware of any of those patients’ outcome in the subsequent year. We will show every care manager a different subset of 40 patients and proceed in 3 steps:

Step 1: For every patient, we will present the historical de-identified patient attributes and the prediction result to the care manager and ask him/her to record the enrollment decision and interventions, if any, that he/she plans to use on the patient. For the historical patient attributes, we will show the static attributes’ values at the top, followed by the longitudinal attributes’ values in reverse chronological order. No care manager will see any automatic explanation in this step.Step 2: For every patient, we will present the automatic explanations and their linked interventions to the care manager and survey him/her using both semistructured and open-ended questions. The automatic explanations will appear as a list of association rules. Below each rule is the list of interventions linked to the rule. The questions will include whether these explanations would change the enrollment decision for the patient, whether he/she believes they would improve care plan quality, their usefulness on a 1 to 7 scale with anchors of not at all/very useful, and their perceived trustworthiness on a 1 to 7 scale with anchors of not at all/completely. Our questionnaire will embrace a text field for writing comments.Step 3: We will use the standard Technology Acceptance Model (TAM) satisfaction questionnaire [107] to survey the care manager about the automatic explanations. A technology is unimportant unless people will accept and use it. Developed based on multiple well-accepted behavioral theories, TAM is the most widely adopted model of people’s acceptance and usage of a technology. The TAM satisfaction questionnaire will measure the perceived usefulness and the perceived ease of use of automatic explanations. Perceived usefulness is known to link strongly to future usage intentions and to actual function usage [108,109]. Multiple studies have demonstrated the validity and reliability of the TAM satisfaction questionnaire [110,111].

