#### Procedures

We will randomly partition the 10 care managers into 2 disjoint groups: the intervention group and the control group. Each group has 5 care managers. From the IH data in the 13th year, we will randomly select 200 IH COPD patients who used the hospital in the subsequent year and whose data are unused in Experiment 1 and automatically explain the prediction results of the best IH model built in Aim 4. For each group, we will show every care manager in the group a different subset of 40 patients. With random assignment, each patient is shown to 2 care managers, one in the intervention group and the other in the control group. In the control group, for every patient, we will show the care manager the historical de-identified patient attributes and the prediction result but no automatic explanation. In the intervention group, for every patient, we will show the care manager the historical de-identified patient attributes, the prediction result, the automatic explanations, and their linked interventions. In both groups, we will ask the care managers to record their enrollment decisions.

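### Experiment 2 compares two unstratified groups of five care managers and does not use the no-explanation enrolment rate that Experiment 1 already records for each manager

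*Protocol article*

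**What the plan says.** All references are to the protocol article, Methods, Aim 5.

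- **Subject Recruitment:** "we will recruit 10 care managers", from about 25 available. On selection: "We will adopt purposeful sampling to ensure adequate variability in work experience".
- **Experiment 1, Procedures:** "We will show every care manager a different subset of 40 patients". In Step 1 the manager sees the patient's history and the model's prediction, and the team will "ask him/her to record the enrollment decision and interventions, if any, that he/she plans to use on the patient". The article adds: "No care manager will see any automatic explanation in this step".
- **Experiment 2, Procedures:** the allocation is described as "We will randomly partition the 10 care managers into 2 disjoint groups: the intervention group and the control group". The split is fixed at five a side, and no stratification, matching or minimisation is named. The 200 patients are ones "whose data are unused in Experiment 1", and each is shown to one manager in each group. The control group sees history and prediction without explanations, the same information as in Step 1.
- **Experiment 2, Analysis:** a random effect logistic model compares enrolment decisions between the groups and allows for correlation within manager and within patient. No manager-level covariate is named.
- **Experiment 2, Justification of the Sample Size:** with an intra-class correlation of 0.1 within manager and within patient, the 400 decisions count as 74 independent ones.

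**The concern.** The unit of allocation is the manager, and there are only five per group. Managers who differ in their general readiness to enrol will, by chance, be unevenly spread over two groups of that size, and that spread is the main source of error in the comparison. The introduction (Gap 3) itself says that practice varies widely across care managers.

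Step 1 of Experiment 1 measures that readiness directly: 40 decisions per manager, under the control condition of Experiment 2, before any explanation is seen. It is a baseline value of the Experiment 2 outcome. The article uses it in neither the allocation nor the model.

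What is at stake is precision. An experiment of this size can miss a sizeable effect, and its one estimate will be hard to interpret. Analysis can adjust for the baseline later, but the allocation cannot be redone once the experiment has run.

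**Working it through.** **Inputs from the article:** 10 managers, 5 per group; 40 decisions per manager in Step 1 and 40 in Experiment 2; intra-class correlation (ICC) 0.1 within manager and within patient; 74 effective instances; 2-sided 5% level.

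**Assumptions, not in the article:** enrolment rate about 50%; log-odds effect 1.0 (odds ratio 2.7); stability, meaning the correlation of a manager's enrolment tendency between the two experiments, shown over a range.

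**1. Reproduce the plan's figure.**
- Manager part of the design effect: 1 + 39 × 0.1 = 4.9.
- Patient part: 1 + 1 × 0.1 = 1.1.
- Product: 5.39, and 400 / 5.39 = 74.2. This matches the stated 74, so nearly all of the plan's own loss of information comes from managers.

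**2. Chance imbalance between groups.**
- SD of managers' true rates at 50%: √(0.1 × 0.25) = 0.158.
- SD of the difference between two means of five: 0.158 × √(2/5) = 0.100.
- Probability that the groups differ by more than 10 points with no intervention effect: 32% (21% if enrolment is 20% or 80%).

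**3. How well Step 1 measures a manager's tendency.**
- Reliability of a 40-patient rate: 0.1 / (0.1 + 0.9/40) = 0.816.
- Correlation of the Step 1 rate with the Experiment 2 rate: r = 0.816 × stability. Adjustment multiplies the error variance by 1 − r².

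| Stability | r | 1 − r² | Effective n, 74.2/(1 − r²) |
|---|---|---|---|
| 1.0 | 0.816 | 0.334 | 222 |
| 0.8 | 0.653 | 0.574 | 129 |
| 0.6 | 0.490 | 0.760 | 98 |
| 0.4 | 0.327 | 0.893 | 83 |
| 0 | 0 | 1 | 74 |

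**4. Detectable difference** (80% power, t distribution, 8 degrees of freedom unadjusted and 7 adjusted, manager-level rates).
- Variance of the group difference: (2/5) × 0.25 × 4.9/40 = 0.01225, so SD 0.111.
- Unadjusted: 35 percentage points.
- Adjusted: 21 points at stability 1.0 and 31 points at 0.6.

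**5. Simulated power.** Crossed manager and patient effects; manager-level analysis; unstratified split without a covariate v pairing on the Step 1 rate plus that rate as covariate.

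| Stability | Stated allocation, no covariate | Pairing + covariate |
|---|---|---|
| 1.0 | 49% | 80% |
| 0.8 | 49% | 64% |
| 0.6 | 48% | 54% |
| 0.5 | 47% | 52% |
| 0 | 47% | 46% |

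Type I error was near 5% for both. Pairing followed by an unadjusted test was conservative and gained no power. The covariate without pairing lost about 5 points of power at stability 0 (54% v 49%, at odds ratio 3); with pairing the loss is 1 to 2 points.

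**The case against.** The strongest reply is that nothing here is an error. Random allocation with a model that carries manager and patient random effects is a valid design, and a fuller plan might name stratification factors or covariates. The validity point stands. The second point stands only in part: the article sets out both the allocation and the model, and neither uses a baseline that it collects.

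A reader might infer more than the documents support:

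- **That chance imbalance will pass for an effect.** It will not do so more often than the nominal level. Between-manager variation is part of the error term, and simulated type I error without the covariate was 4.9% to 5.6%. The harm is lost precision.
- **That the comparison is wholly unadjusted.** It allows for both kinds of correlation, and patient mix is balanced because each patient appears once in each group. Only a manager-level baseline is absent.
- **That selecting for varied experience widens the between-manager variance.** Nothing in the article links work experience to enrolment tendency, and varied experience is a reasonable aim for the qualitative work.
- **That Step 1 data would remove most of the noise.** This holds only near full stability. At 0.8 the variance falls by 43% (1 − 0.574) and at 0.6 by 24%. Step 2 then shows every manager explanations for the same 40 patients, which may itself shift later decisions and lower stability.

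Two limits on the figures also stand. The simulation analyses manager-level rates rather than fitting the planned logistic model, and its effect size is assumed. At the article's own target of a 9.7% increase in odds, simulated power is about 5% to 6% with or without the covariate, so this change does not rescue that target.

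**Conclusion.** The point holds as an inexpensive improvement in precision, not as a flaw in validity. The article collects a baseline measure of the Experiment 2 outcome on the very units it randomises and uses it in neither allocation nor analysis, although manager clustering dominates the error.

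At the plan's ICC of 0.1, and assuming 50% enrolment and a log-odds effect of 1.0, using the baseline raises power from about 48% to between 52% and 80% for stabilities from 0.5 to 1.0, and costs 1 to 2 points if stability is 0. Stability is the deciding unknown, and the documents give no figure for it. That Experiment 1 comes before Experiment 2 is implied by the rule on unused patients but not stated outright.

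**What to change.** - State that Step 1 of Experiment 1 is complete for all 10 managers before Experiment 2 allocation.
- Rank the managers by Step 1 enrolment rate and randomise within adjacent pairs, which keeps the 5 v 5 split.
- Add the Step 1 rate as a covariate to the random effect logistic model, with small-sample inference for 10 clusters. Do not pair without the covariate.
- Do the same for the 10 physicians.

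Cost: no new patients, managers or measurements. The covariate uses one of 8 manager-level degrees of freedom, and allocation must wait until Step 1 is finished.
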